# PROTOCOL SUMMARY

## Synopsis

| **Title:** | Skills to Enhance Positivity in Adolescents at Risk for Suicide |
| --- | --- |
| **Grant Number:** | MH123556-01A1 |
| **Study Description:** | The purpose of this study is to examine the effectiveness of the Skills to Enhance Positivity (STEP) intervention in reducing suicidal behaviors in adolescents who have been admitted to an inpatient psychiatric unit due to suicide risk. |
| **Objectives:** | Primary Objective: Examine the effectiveness of STEP in reducing suicidal events (suicide attempt or emergency intervention to intercede attempt), active SI (with intent or plan), and depression at 6-month follow-up (primary endpoint outcomes) and suicidal events at 12-month follow-up (distal, endpoint outcome).  Secondary Objective: Examine engagement of the hypothesized mechanisms (attention to positive and negative affect) at the 3- and 6-month follow-up.  Tertiary Objective: Examine whether hypothesized mechanisms mediate reduction of suicidal events and ideation. |
| **Endpoints:** | Primary Endpoint: Suicidal events, active suicidal ideation, and depression at 6 month follow-up.  Distal Primary Endpoint: Suicidal events at 12 month follow-up.  Secondary Endpoint: Attention to Positive Affect and Negative Affect at 6 month follow-up. |
| **Study Population:** | Adolescents, regardless of sex, gender, race, and ethnicity, between the ages of 12-18, who have been hospitalized due to suicide risk (i.e., a suicide attempt or suicidal ideation) will be recruited for study participation from three adolescent units at Boston Children’s Hospital (Boston, MA), Butler Hospital (Providence, RI), & Bradley Hospital (Providence, RI). Target recruitment is 216. |
|  |  |
| **Phase or Stage:** | Phase III |
| **Description of Sites/Facilities Enrolling Participants:** | Three sites, all in the United States, will be enrolling participants: 1) the adolescent inpatient unit at Boston Children’s Hospital; 2) the adolescent unit of Butler Hospital; and 3) the adolescent inpatient unit at Bradley Hospital |

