# OBJECTIVES AND ENDPOINTS

| OBJECTIVES | ENDPOINTS | JUSTIFICATION FOR ENDPOINTS | PUTATIVE MECHANISMS OF ACTION |
| --- | --- | --- | --- |
| Primary |  |  |  |
| To examine the effectiveness of STEP in reducing suicidal events (suicide attempt or emergency intervention to intercede attempt, i.e. ED evaluation or psychiatric hospitalization), active suicidal ideation (with intent or plan), and depression, compared to ETAU. | Suicidal events and active suicidal ideation as assessed by the Columbia-Suicide Severity Rating Scale (C-SSRS) interview, and depression as assessed by the Beck Depression Inventory (BDI-II) at 6 month follow-up (primary endpoint) and suicidal events at 12 month follow-up (secondary endpoint) | Six-month follow-up is selected as the primary end-point time as numerous studies have shown this to be a particularly high-risk time for repeat suicidal behaviors. Twelve months allow us to assess the long-term effectiveness. | NA |
| Secondary |  |  |  |
| To examine engagement of the hypothesized mechanisms of positive affect (PA) and negative affect (NA). | Attention to PA and NA as assessed by implicit cognitive tasks and self-report forms (See 1.3) at 3 month follow-up (primary) and 6 month follow-up (secondary) endpoint. | PA and NA are hypothesized to be causal mechanisms. Thus these assessments will see if we engaged our treatment target of PA and NA. | PA and NA are hypothesized to be causal mechanisms. |
| Tertiary/Exploratory |  |  |  |
| To examine whether hypothesized mechanisms mediate reduction of suicidal events and ideation. | Attention to PA and NA as assessed by implicit cognitive tasks and self-report forms (See 1.3) at 3 month follow-up (primary) and 6 month follow-up (secondary) endpoint. | The PA and NA assessments, using both implicit and subjective assessments, will be examined as mediators. Specifically, PA and NA at 3 month f/u is hypothesized to mediate the relationship between study intervention and clinical outcomes at the 6 month f/u; and PA and NA at 6 month f/u is hypothesized to mediate the relationship between study intervention and clinical outcomes at the 12 month f/u. | PA and NA will be examined as mediators. |

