# STUDY DESIGN

## Overall Design

This is a randomized controlled trial (RCT) of Skills to Enhance Positivity (STEP) vs. Enhanced Treatment as Usual (ETAU). It is hypothesized that those randomized to STEP, compared to ETAU, will have lower rates of suicide events, active SI, and depression over the 6-month follow-up period (primary endpoint), and over 12 months of follow-up (secondary endpoint). Recruitment will occur at three sites, Boston Children’s Hospital, Butler Hospital, and Bradley Hospital. Eligible individuals who consent to participate will be randomly assigned to either STEP or ETAU in a 1:1 allocation after the baseline assessment. Co-I [name] will prepare a stratified [by study site, history of SB (yes/no), and sexual or gender minority (yes/no)} randomization schedule using random blocks and provide this to our REDCap administrator; study staff will not have access to randomization tables). Research staff will be able to obtain assignments in real time once consent and stratification variable information are recorded. We use random block sizes to prevent guessing of pending treatment assignments.

The study intervention, Skills to Enhance Positivity (STEP), is an adjunctive psychosocial intervention that involves 4 in-person sessions during a participant’s inpatient admission, followed by three months of text or email messaging for mood monitoring and skills delivery. (If participant has a shorter length of stay or is discharging early, the STEP sessions may be shortened so that the intervention can be delivered prior to discharge). The sessions and skills delivered via the text or email messages focus on the functions of positive affect and ways to bring greater attention to and awareness of positive emotions and experiences on a daily basis. Four videos with content derived directly from the treatment manual will be used to support the delivery of the STEP skills that are covered in the in-person sessions.

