Suicidal Ideation. Active SI will also be assessed using the C-SSRS; specifically, we will assess active SI, operationalized by a score of 3 or higher on the suicide ideation questions of C-SSRS, using their highest level of ideation during the worst week of the f/u interval. We will also obtain weekly ratings of SI using the methodology of the *Longitudinal Interval Follow-Up Evaluation* (LIFE)(54), at the 3-, 6-, and 12 month f/u’s. The LIFE format asks participants to rate their level of SI in the preceding interval on a 6-point psychiatric status rating (PSR) scale. This methodology, which yields weekly scores, as applied to the assessment of SI in adolescents has been successfully implemented in at least three NIMH-funded studies for which MPI [name] was a PI (K23MH069904, MH090137, MH059929). Our data from adolescents admitted to the Butler adolescent unit and followed for 6 months after discharge (K23MH069904) demonstrate a good range of variability in SI PSR scores (e.g., 20% clinically significant SI; 36% no weeks clinically significant SI, 6% chronic, unremitting, high levels of SI for all weeks of f/u). We will also administer the Suicide Ideation Questionnaire, a 30-item self-report instrument with good psychometric properties in adolescents.

Diagnostic / Symptom Rating Scales. Depression will be assessed by the *Beck Depression Inventory (BDI-II)* (39) administered to both adolescent and parent (about teen). The BDI-II is a widely used 21-item measure with excellent psychometric properties (55), and also validated in Spanish. Cronbach’s α in the pilot sample was 0.90 in adolescents and 0.89 in adults. Alcohol use will be assessed using the Alcohol Use Disorder Identification Test (AUDIT) and drug use will be assessed using the Drug Use Disorder Identification Test (DUDIT). Other symptom rating scales include the Borderline Evaluation of Severity Over Time (BEST) and the Columbia Impairment Scale (CIS). All are self-reports and assessments will be administered at baseline, 3-, 6-, and 12-months f/u.

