**Aim 1A-C:** *Examine the effectiveness of STEP in reducing suicidal events, active SI*, *and depression at 3- and 6-month follow-up (f/u).* We hypothesize that those randomized to STEP, compared to ETAU, will have (**H1A**) lower prevalence of suicidal events (operationalized as either a suicide attempt or emergency intervention to intercede when there is a high likelihood of an attempt) **(H1B**) lower prevalence of time with active SI (operationalized as SI with intent or plan), and (**H1C**) lower level of depressive symptoms, over the 6-month follow-up period. Aim 1 analyses will use a repeated measures design and a multilevel or mixed effect modeling framework. For H1A and H1B, the outcome is binary and a mixed effect logistic regression model will be used. For H1C, the outcome is continuous and a mixed effect general linear model will be used. For H1B, the outcomes are repeatedly observed over follow-up weeks within the 6M timeframe (24 weeks), and can yield a categorical (active SI, worst week) outcome, which would be analyzed like H1A or a continuous (proportion of weeks with active SI) outcome, which would be analyzed differently like H1C. For H1A and H1C the outcome is observed twice at the scheduled follow-ups (3M, 6M). For all hypotheses, we will treat the individual as the random effect. Treatment effects will be estimated as the weighted average of the differences between ETAU and STEP groups over all follow-up times, adjusting for follow-up time.

In secondary analyses to identify potential mechanisms (i.e. mediators) of treatment effectiveness that occur after randomization, we will repeat these analyses using medication use and psychosocial treatment as covariates.

In secondary analyses, payor data will be examined as a potential moderator or predictor of these outcomes.

In secondary analyses, the patterns of change in depressed mood (BDI scores) will be evaluated using random effects models for longitudinal data.

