***Sample size and statistical power considerations:*** We determined minimal detectable effect sizes using Monte Carlo methods. This involved generating 1,001 simulated data sets representing our hypothesized effects, and our assumptions of a 10% loss by 3M and another 10% loss by 6M follow-up. We assumed repeated measures of depressive symptoms and the propensity to active suicidal ideation and suicidal events were all correlated at *r* = .5. Across the simulated data sets, we compute power as the proportion of replicates returning a significant effect in the hypothesized direction. Results of these models are summarized in Table 3, above. We summarize effects in terms of Cohen’s effect size statistics for clear expression of the minimum detectable effects. For H1A, H1B, and H1C, we will have sufficient power to detect small-to-medium effect sizes (.46, .31, .35, respectively).

**Aim 1D:** *Examine the effectiveness of STEP in reducing suicidal events at the 12-month f/u.* We hypothesize that those randomized to STEP, compared to ETAU, will have lower rates of suicidal events at the 12-month, long term f/u. This hypothesis will be tested to evaluate the durability of STEP effects over long-term follow-up. We expect to see the full effect of STEP at the 6M follow-up. This hypothesis will be evaluated with logistic regression, and not as part of the repeated measures analysis specified in H1A. If the effect continues through 12M, we will have 80% power to detect a difference in event rates of 38% ETAU and 17% STEP at the 12M follow-up.

In secondary analyses, the within-person frequency of suicidal events and suicidal ideation will be analyzed. These analyses will use (zero inflated) negative binomial regression models to account for the anticipated extreme skew of these outcomes.

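### The detectable effect printed for H1B (.31) fits a 24-week weekly model, not the C-SSRS worst-week outcome that the protocol defines as the active-SI primary endpoint

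*Protocol*

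**What the plan says.** The Aim 1A-C sample size paragraph of section 9 gives one set of assumptions for all three hypotheses: "our assumptions of a 10% loss by 3M and another 10% loss by 6M follow-up", and "repeated measures of depressive symptoms and the propensity to active suicidal ideation and suicidal events were all correlated at" r = .5. It then prints three detectable effects: "For H1A, H1B, and H1C, we will have sufficient power to detect small-to-medium effect sizes (.46, .31, .35, respectively". It refers to Table 3 for the results and describes the metric only as Cohen's effect size statistics.

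The Aim 1A-C analysis paragraph calls H1A and H1B binary outcomes for a mixed logistic model. It says H1A and H1C are observed twice (3M, 6M) and H1B over 24 follow-up weeks. The H1B data, it adds, "can yield a categorical (active SI, worst week) outcome, which would be analyzed like H1A or a continuous" proportion-of-weeks outcome, handled like H1C. It does not choose between them.

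Section 3 sets the primary endpoint: "Suicidal events and active suicidal ideation as assessed by the Columbia-Suicide Severity Rating Scale (C-SSRS) interview". Section 8.1 defines active SI as a C-SSRS ideation score of 3 or higher, "using their highest level of ideation during the worst week of the f/u interval". The weekly ratings come from a different instrument, the LIFE, which section 8.1 introduces as an additional measure. The Schedule of Activities places the C-SSRS at baseline, 3, 6 and 12 months.

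**The concern.** N, loss and correlation are common to the three hypotheses. An H1B outcome analysed like H1A should therefore have a detectable effect near H1A's .46, and one analysed like H1C a figure near .35. The printed .31 is smaller than both. It makes active SI look like the most sensitive of the three Aim 1 tests, whereas the endpoint as defined has no more observations per person than H1A. A reader of a null active-SI result could then take an effect of .31 as excluded when the trial had appreciably less than the implied power to detect it.

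**Working it through.** **Inputs.** Total N: "Target recruitment is 216" (Synopsis). Allocation: "randomly assigned to either STEP or ETAU in a 1:1 allocation after the baseline assessment" (Overall Design), so 108 per arm. Losses of 10% and then another 10% leave 108 × .9 = 97.2 per arm at 3M and 108 × .8 = 86.4 at 6M. Thus 86.4 contribute the whole follow-up and 10.8 the first half only. r = .5, on the latent propensity for the binary outcomes. Assumed, because section 9 gives no number for H1A-C: 80% power (printed for Aim 1D) and two-sided 5%.

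**Formula.** MDE = (1.960 + 0.842) × √(2/I), where per-arm information I sums m/(1 + (m − 1)ρ) over participants with m observations each.

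**Reproducing H1C.** Two continuous visits, ρ = .5: I = 86.4 × 2/1.5 + 10.8 = 126.0. MDE = 2.802 × √(2/126.0) = .353. Printed: .35.

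**Reproducing H1A.** For a binary outcome, ρ is the phi coefficient implied by a latent correlation of .5 (about .31 at a 27.5% rate, .33 at 50%). At 27.5%: I = 86.4 × 2/1.31 + 10.8 = 142.7, so MDE = .332 on h. To convert to latent d, divide by φ(z)/√(p(1 − p)) = .334/.447 = .747, which gives .44. Event rates of 20-28% give .44-.47. Printed: .46. Simulated power at d = .46 is 76-84% for rates of 25-50%.

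**Reproducing H1B.** Twenty-four weekly binary values at 50% prevalence: I = 86.4 × 24/(1 + 23/3) + 10.8 × 12/(1 + 11/3) = 239.3 + 27.8 = 267.0. MDE = .243 on h; dividing by .798 gives latent d = .30. Weekly prevalence of 28-50% gives .30-.32. Printed: .31. Simulated power at .31 is 78-81% for prevalence of 38-50%. Twenty-four continuous values give .29 with the stated losses (.32 with 81 per arm).

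**Can fewer observations give .31?** Power at .31 is Φ(2.802 × .31/MDE − 1.960).

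| Outcome | MDE at 80% | Power at .31 |
|---|---|---|
| Binary, two visits, latent d (rates 17-50%) | .42-.49 | about 47-54% (simulated, rates 25-50%) |
| Binary, two visits, Cohen's h | about .33 | about 72-74% |
| Continuous, two visits | .35 | about 70% |
| One value per person (86 per arm) | .43 | 53% |

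The printed figures alone agree. If .46 has 80% power, .31 has Φ(2.802 × .31/.46 − 1.960) = Φ(−.07) = 47%. If .35 has 80%, .31 has Φ(.52) = 70%. A one-sided test with two continuous visits gives (1.645 + 0.842) × √(2/126.0) = .31, but H1C would then be .31 too, not .35.

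**Same underlying weekly effect.** The table applies .31 on each outcome's own scale. If the true effect is instead one weekly latent shift of .31, simulated power is:

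| Weekly prevalence | 24-week model | Proportion of weeks | Worst week, two intervals | One worst week |
|---|---|---|---|---|
| 15% | 70% | 64-70% | 67% | 54% |
| 20% | 72% | 68-72% | 66% | 51% |

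At 38% weekly prevalence, the 24-week model has 79% and the two-interval worst week 56%.

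**The case against.** The strongest reply is that .31 is correctly computed for H1B as section 9 first describes it. The hypothesis concerns prevalence of time with active SI, the base model is a mixed logistic regression, and the data are 24 weekly observations; worst week and proportion of weeks are only summaries those data can yield. This stands: .31 reproduces for a model the protocol names. It does not answer sections 3 and 8.1, where the primary endpoint is the C-SSRS worst week and the weekly LIFE ratings are additional.

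Second, Table 3 may state which version was simulated and on what metric. This also stands. The attribution to the weekly model is an inference, and the absence of the table is not held against the plan.

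Third, H1A and H1B may not share a scale. The Background gives the pilot's suicidal events as h and its active SI as d. Section 9 calls the H1A and H1D detectable effects similar, and H1D's 38% against 17% is h = .48, so .46 could be an h. The scaling from .46 to 47% power would then fail. Two binary visits at r = .5 give .33 on h and reproduce .46 only on latent d, which favours the latent scale without proving it. On h the gap is modest: .33 against .31.

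Fourth, the loss is partly a matter of units. For the same weekly effect, proportion of weeks loses little, and a two-interval worst week loses little at 15-20% weekly prevalence. This stands and limits the size of the point.

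**Conclusion.** The point holds in a limited form. The printed .31 is not a detectable effect for the active-SI endpoint defined in sections 3 and 8.1. At two-sided 5% and 80% power, no version tried with one or two observations per person reproduces it alongside .46 and .35. For the worst-week outcome seen twice, power at .31 is about 47-54% on the scale that reproduces H1A's figure and about 72-74% on Cohen's h. For a continuous outcome seen twice it is about 70%, and for one value per person about 53%. These figures rest on the assumed alpha and power target, and on r = .5 acting on the latent scale for binary outcomes.

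A reader might infer three stronger things that the documents do not support. One is that .31 is an arithmetic error; it fits the weekly model in section 9. Another is that the trial has only about an even chance on active SI; that takes the low end of a range that depends on an unnamed scale. The third is that .31 should simply become about .45; that would choose the outcome and the metric for the sponsor. Nor does section 9 derive N from .31 or say that a null result would exclude it. The risk is over-reading, not a mis-sized trial.

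**What to change.** In the Aim 1A-C text of section 9, state which H1B outcome is primary, consistent with sections 3 and 8.1. Rerun the existing simulation for that outcome and print its detectable effect with the scale named (latent d, h or other), in the text and in Table 3 if not already there. If the outcome is the C-SSRS worst week at 3M and 6M, expect essentially the H1A figure on H1A's scale. If it is proportion of weeks analysed like H1C, expect about .35 for two intervals or about .43 for one value per person, in SDs of that outcome. Keep .31 only with a label saying that it applies to the week-by-week LIFE model.

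The cost is one simulation rerun and, if the C-SSRS worst week is kept, one less favourable printed figure. Sample size and study procedures are unaffected.

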Implicit Positive and Negative Affect. A dot probe task will assess for attention bias toward negative or positive stimuli (56). The task will comprise 256 very brief trials (approximately 10 minutes total time) consisting of the various combinations of probe type (the letter E or F), probe position (top or bottom), and emotion type (Neutral, Positive, Negative). The stimuli used for this task will be from the same sets of standardized sets of emotional and neutral words used in our pilot project. During the task, gaze will be monitored using a Tobii Pro Nano mobile eye tracker. Each trial begins with a fixation cross that remains on the screen until the participant makes a fixation on the cross. Then, an emotional-neutral word pair is shown on the screen for 500 ms. After this, a probe (E or F) appears in the location of one of the words. The probe remains on the screen until the participant identifies which letter appeared and presses the corresponding button on the keyboard. To facilitate comparison with previous research, we will compute standard attention bias scores reflecting the difference in reaction times to probes following emotional versus neutral words. However, given concerns about reaction time-based indices of attentional bias (57-60), our primary analyses will be indices of initial orienting (location and latency of first fixation) and sustained attention (overall gaze duration) derived from eye-tracking, which have stronger psychometric properties (58, 59). We will also assess attention to PA using the IPANAT (49). This is an indirect assessment of automatic activation of affective representations that utilizes artificial words paired with positive and negative words. Factor analyses of ratings yield two independent factors interpreted as positive and negative. A single score of implicit affect (positive, negative) reflects both state and trait variance. The IPANAT has demonstrated strong convergent and discriminant validity, and adequate internal consistency and test-retest reliability. A series of experiments found a strong trait component (r = .60) but also susceptibility to environmental changes (e.g., affect induction) and is strongly associated with transient explicit PA and NA. Our two proposed tasks to be administered at baseline, 3-, and 6-month f/u, can assess our primary mechanism of PA, as well as our secondary mechanism of NA.

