# STATISTICAL CONSIDERATIONS

**Data Analyses.** In this section, we describe aim by aim the proposed method of data analysis and sample size considerations. **Scientific rigor** is enhanced and maintained by: 1) randomization procedures, 2) having assessment staff blind to condition, 3) multiple modalities of assessment, 4) comprehensive retention procedures, 5) preliminary analyses, 6) missing data procedures, and 7) data analytic strategies that are consistent with best practices for the analysis of randomized clinical trials as embodied in the Consolidated Standards of Reporting Trials (CONSORT) statement (75)**.** Additionally, relevant biological variables, specifically sex, are considered in the experimental design. We do not have a priori hypotheses regarding sex differences in the effect of STEP on our study outcomes. Accordingly, and in agreement with NIH guidance on this topic our plan is to separately tabulate results by sex but test our main hypotheses in a sample with both sexes combined (<http://orwh.od.nih.gov/sexinscience/overview/pdf/NOT-OD-15-102_Guidance.pdf>). Finally, by collecting implementation outcome data, we will be able to identify and develop implementation strategies to encourage greater uptake and adoption of STEP in a future R01 implementation trial. As all our hypotheses are pre-specified, no adjustment for multiplicity will be used.

[figure not shown]
Our randomization procedures include stratification on important predictors of the main outcome variable and are automated and protected from inadvertently revealing treatment assignment order to staff. This will help ensure the blinding of assessment staff to treatment condition. Our plan for how missing data will be

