**Aim 2:** *Examine engagement of the hypothesized mechanisms at the 3- and 6-month f/u.* We hypothesize that those randomized to STEP, compared to ETAU, will have*:* **H2A:** higher attention to positive affect, assessed by implicit tasks; **H2B**: Increased gratitude and satisfaction with life, assessed by self-report; **H2C**: lower attention to negative affect, assessed by implicit tasks and self-report. Aim 2 analyses will use a repeated measures design and a multilevel or mixed effect modeling framework. For H2A, H2B, and H2C, the outcomes are continuous and a mixed effect general linear model will be used. Outcomes are repeatedly observed over follow-up and assessed at the scheduled follow-up (3M, 6M). For all hypotheses, we will treat the individual as the random effect. Treatment effects will be estimated as the weighted average of the differences between ETAU and STEP groups overall follow-up times, adjusting for follow-up time. ***Sample size and statistical power considerations***: As with H1, we determined minimal detectable effect sizes using Monte Carlo methods. This involved generating 1,001 simulated data sets representing our hypothesized effects, and our assumptions of a 10% loss by 3M and another 10% loss by 6M follow-up. We assumed repeated measures of the measures assessing the mechanisms (attention to positive affect, gratitude and satisfaction with life, and attention to negative affect) to have a stronger correlation within a respondent over time than the Aim 1 outcomes, and assumed *r* = .75, which results in a smaller effective sample size. Across the simulated data sets, we compute power as the proportion of replicates returning a significant effect in the hypothesized direction. Results of these models are summarized in Table 3, above. We summarize effects in terms of Cohen’s effect size statistics for clear expression of the minimum detectable effects. For Aim 2 outcomes, we will have sufficient power to detect small-to-medium effect sizes (*d* = .39).

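### Aim 2 rules out multiplicity adjustment but names no deciding measure, although H2A rests on up to four measures and H2C on up to five

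*Protocol*

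**What the plan says.** Section 9 of the protocol states Aim 2 as three directional hypotheses. H2A is "higher attention to positive affect, assessed by implicit tasks". H2B is "Increased gratitude and satisfaction with life, assessed by self-report". H2C is lower attention to negative affect, on implicit tasks and on self-report. The outcomes are analysed with a mixed linear model that gives one treatment effect averaged over the 3- and 6-month visits. A single detectable effect, d = .39, is quoted for all Aim 2 outcomes.

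Section 8.1 defines the implicit measures. For the dot probe, "our primary analyses will be indices of initial orienting (location and latency of first fixation) and sustained attention (overall gaze duration) derived from eye-tracking"; reaction-time bias scores are kept for comparison with earlier research. It then adds: "We will also assess attention to PA using the IPANAT". That test gives a positive and a negative score. The two tasks, it says, "can assess our primary mechanism of PA, as well as our secondary mechanism of NA".

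The secondary endpoint in the Objectives and Endpoints table is "Attention to PA and NA as assessed by implicit cognitive tasks and self-report forms".

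On multiplicity, Section 9 is explicit: "As all our hypotheses are pre-specified, no adjustment for multiplicity will be used".

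**The concern.** The reason given for not adjusting does not fit Aim 2. Writing a hypothesis down in advance stops new hypotheses being added later. It does not limit error when one hypothesis can be confirmed by any of several measures, each tested at the full significance level. Section 9 does not say whether H2A needs one particular measure, all of them or any of them.

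The pilot shows how such a claim can arise. The Background section reports one significant between-group difference on the dot probe, at 3 months (p = .048). The groups did not differ on that task at the end of treatment, and no self-report measure separated them. From this the Study Rationale concludes that target engagement was demonstrated. Aim 2 leaves the same route open with more measures.

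At stake is the trial's statement that STEP engaged its target, and a clear basis for choosing among mediators in Aim 3.

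**Working it through.** **1. Count the measures (Sections 8.1 and 9).**
- H2A: first-fixation location, first-fixation latency and gaze duration for positive words, plus IPANAT positive = 3 + 1 = 4.
- H2B: gratitude (GQ-6) and satisfaction with life (SWLS) = 2.
- H2C: the three gaze indices for negative words, IPANAT negative and mDES negative = 3 + 1 + 1 = 5.
- The mDES positive score falls within the endpoint in the Objectives and Endpoints table but under no Aim 2 hypothesis. It is not counted.
- Reaction-time scores are not counted, because they are kept for comparison only.
- Visits add no tests, because Section 9 pools them.

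The counts of four and five are upper readings. Section 8.1 does not say whether location and latency are tested separately or combined.

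**2. Reproduce d = .39.** Inputs from the protocol: 216 participants at 1:1, so 108 per arm; 10% loss by 3 months and another 10% by 6 months, so 97.2 and 86.4 per arm; within-person correlation .75. Assumed: two-sided alpha .05, since no number is stated (the 1-(a/2) term in the Aim 1D formula implies two-sided testing), and 80% power as stated for Aim 1D.
- Information per arm = 86.4 × 2/(1 + .75) + (97.2 − 86.4) = 98.7 + 10.8 = 109.5.
- SE = √(2/109.5) = .135.
- Detectable d = (1.960 + .842) × .135 = .379.
- Simpler version with about 92 per arm at both visits: 2.802 × √(1.75/92) = .386.
- With 81 per arm at both visits: .412.

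The stated .39 lies inside this range. It is therefore a figure for one measure at unadjusted alpha.

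**3. False-positive chance if any one measure suffices and STEP changes nothing.** With k independent measures the two-sided rate is 1 − .95^k. In the favourable direction it is 1 − .975^k.
- H2A: 1 − .95⁴ = 18.5%; 1 − .975⁴ = 9.6%.
- H2C: 1 − .95⁵ = 22.6%; 1 − .975⁵ = 11.9%.

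The measures are probably correlated, and the protocol gives no correlations between them. The other rows come from 400,000 draws of equicorrelated normal statistics with critical value 1.96.

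| Assumed correlation | H2A favourable | H2A two-sided | H2C favourable | H2C two-sided |
|---|---|---|---|---|
| 0 | 9.6% | 18.5% | 11.9% | 22.6% |
| .3 | 8.7% | 17.4% | 10.5% | 20.8% |
| .5 | 7.8% | 15.6% | 9.2% | 18.3% |
| .7 | 6.5% | 13.0% | 7.4% | 14.9% |
| Nominal | 2.5% | 5% | 2.5% | 5% |

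The favourable columns matter most. The hypotheses are directional, and the protocol's power simulation counts only effects in the hypothesised direction.

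**4. Price of adjustment within H2A.** The first Holm step over four measures uses alpha .05/4 = .0125, critical value 2.498.
- Detectable d = (2.498 + .842) × .135 = .451, or 3.340 × √(1.75/92) = .461 in the simpler version.
- Power at d = .39 for a given measure at that step: Φ(.39/.135 − 2.498) ≈ 65%, against 82% unadjusted.
- Over the five H2C measures, alpha = .01 and detectable d is .462.

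**The case against.** The strongest reply is that choosing among gaze indices for a secondary mechanism objective is detail that a statistical analysis plan normally settles, and that plan is not shown. Section 9 also allows the analysis to be modified after review. This would succeed if the protocol were merely silent. It is not: it rules out adjustment and gives a reason that does not hold where one hypothesis has several measures.

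Second, the any-one-measure rule is not in the protocol. This stands. The error rates above are conditional on that rule. If every measure had to succeed there would be no inflation, and the word *and* in H2B and H2C can be read that way. The defect is that the text leaves both readings open, and the pilot was interpreted the permissive way.

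Third, Table 3, which Section 9 cites for the power results, is not visible, so how it lists the Aim 2 outcomes cannot be checked.

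A reader might also infer more than the document supports:
- *A 43% error rate for Aim 2.* This is 1 − .95¹¹ over all eleven measures. It pools three separately stated hypotheses, assumes independence and counts unfavourable results. It does not measure the problem within one hypothesis.
- *A chance Aim 2 result passes straight into a mediation claim.* Aim 3 needs an arm difference on the mediator but sets no significance gate from Aim 2. It re-estimates those paths in its own model with bootstrap intervals and is labelled exploratory.
- *H2C must be tested only after H2A.* Section 8.1 ranks positive affect above negative affect as a mechanism. It ranks constructs and says nothing about test order.

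**Conclusion.** The point holds in a limited form. The protocol declines adjustment on a ground that does not control error within H2A or H2C, and it supplies no deciding measure in its place. If engagement is claimed from any one favourable measure, the false-positive chance for H2A is about 8% at an assumed correlation of .5 (6.5% to 9.6% for .7 down to 0), roughly three times the nominal 2.5%.

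This rests on a two-sided alpha of .05, on equal correlations between measures, on counting location and latency separately, and on the permissive success rule. None of these is stated in the protocol. The inflation shrinks as the measures become more alike: at a correlation of .9 the H2A figure is 4.7%.

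The consequence is confined to the target-engagement claim. The primary effectiveness conclusions are not affected.

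**What to change.** Amend Aim 2 in Section 9, and the multiplicity sentence in the same section to match:
- **H2A and H2C:** name one deciding measure for each from the protocol's own primary eye-tracking indices (for example, overall gaze duration to positive words for H2A), or apply Holm across the measures within the hypothesis.
- **H2B:** state that both gratitude and satisfaction with life must succeed. This adds no error and keeps the hypothesis.
- **Other measures:** if a single measure is named, report the remaining gaze indices, the IPANAT scores and both mDES scores as supportive, with intervals and no engagement claim of their own. H2C's wording should then say that self-report is supportive.
- **Multiplicity sentence:** replace the appeal to pre-specification with the rule chosen for each Aim 2 hypothesis.

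Gating H2C on H2A and dropping H2B are not required.

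The cost is wording only, with no new data. With one named measure, d = .39 stands. With Holm, the detectable effect at the first step rises to about .45 to .46 for H2A and about .46 for H2C.
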